### Data collection and outcome measures

Baseline data collection is completed prior to randomization and is accomplished by a self-administered survey, anthropometric measurements collected by the study team or obtained from the participant’s clinical care provider as well as blood and urine analysis, specifically for the study or from a recent test requested by the clinical care provider. Table 1 shows the measurement tools used for data collection, the method of collection and time points (baseline, six or 12 months) at which data is collected. Anthropometric measures are collected by project staff specifically trained in accordance with standard clinical measurement methods [21]. Briefly, the left arm circumference is measured to determine the appropriate cuff size for blood pressure (BP) measurement. BP and pulse is measured and recorded three times using the Omron HEM-907 IntelliSense professional digital blood pressure monitor with at least one minute between readings. Height is measured using a portable stadiometer height rod to the nearest 0.5 cm whilst the participant is standing without shoes. Weight is measured to the nearest 0.1kg using a Salter portable weighing scale, model 913. Waist circumference is measured halfway between the lowest rib and the top of the hipbone using the Novel figure finder tape measure. Duplicate waist circumference measurement is undertaken for approximately 10% of the participants for quality assurance. Blood pressure machines and weight scales are calibrated at least weekly. Pathology laboratories providing blood and urine analysis are accredited by the National Association of Testing Authorities (http://www.nata.asn.au/) and all methods for determining HbA1c% are NGSP approved (http://www.ngsp.org/). 

**Table 1 T1:** Measurement domains, survey tools and collection method used at each data collection time point

**Variable**	***Component***	**Measurement tools/Questions**	**Base line**	**6 mth**	**12 mth**	**Type of administration**
Demographic Measures		Age at diagnosis	✓	✓		
		Health Insurance	✓		✓	Postal survey
		Age, Sex, Country of birth, Living Arrangement (Marital status), Education, Income, Employment status,	✓		✓	
		Ethnicity, Health Care Access,	✓		✓	
Clinical Information	*Current Clinical Measures*	On insulin, since when, #/day, Most recent HbA1c,	✓	✓	✓	
		Other medical treatments, past medical history	✓		✓	Postal survey
		List of prescribed medications, last dilated eye				
		exam/retinal photo, foot exam, Past medical history,	✓	✓	✓	
	*Health before, at and since diagnosis*	Pre-diagnosis; at diagnosis and post-diagnosis conditions	✓		✓	Postal survey
	*Anthropometric*	Waist circumference *(Novel Figure Finder Tape Measure)*	✓	✓	✓	Collected by project team /or from clinical care provider (CCP)
		Blood Pressure *(Omron HEM-907 IntelliSense*	✓	✓	✓	
		*professional digital blood pressure monitor)*				
		Weight *(Salter portable weighing scale, model 913)*	✓	✓	✓	
		Height *(Portable Stadiometer Height Rod)*	✓			
	*Pathology*	HbA1c,Total Cholesterol(TC), TC/HDL ratio	✓	✓	✓	Pathology for study/ CCP
		Urine microalbumin, Fasting blood glucose, Trig, HDL, LDL,	✓		✓	
Behavioural	*Physical Activity*	Single physical activity question (# minutes/week)	✓	✓	✓	Postal survey
	*Nutrition*	Cancer Council Food Frequency Questionnaire [22]	✓		✓	FFQ
	*Smoking*	Current/ever smoked/ FFQ /SDSCA	✓	✓	✓	Postal survey
	*Alcohol*	Alcohol days/ quantity/ FFQ	✓	✓	✓	Postal survey
	*Self-care activities*	(SDSCA) Selfcare activities scale with Toobert, Fisher & Glasgow modifications [23,24]	✓	✓	✓	Postal survey
	*Medication*	Morisky 8-item [25,26]	✓	✓	✓	Postal survey
QOL	*Assessment of quality of life*	AQoL-8D [27] and EQ-5D™[28,29]	✓	✓	✓	Postal survey
	*Diabetes Distress*	Diabetes Distress Screening Instrument: DDS4 [30,31]	✓	✓	✓	Postal survey
	*Depression*	PHQ-9 [32]	✓	✓	✓	Postal survey
Mediators and Moderators	*Health literacy*	[33]	✓	✓	✓	Postal survey
	*Non-directive vs directive support*	[12]		✓	✓	
	*Availability & satisfaction with diabetes-support from family, friends & health care team*	[34]	✓	✓	✓	Postal survey
	*Sources of Support*	Who are you supported by?	✓	✓	✓	Postal survey
	*Diabetes Knowledge*	Michigan Diabetes Research and Training Centre with modification to Australian context [35]	✓	✓		Postal survey
	*Self-Efficacy*	Diabetes Self-Efficacy Scale [36]	✓	✓	✓	Postal survey
Use of diabetes services	Health-care utilisation	GP details, Travel time, waiting time	✓	✓		Postal survey
		Insurance, NDSS membership, DA-Vic membership, GP/ specialists/ health professionals visits over past 6 mths, ECG, vaccinations, hospital stays, etc. based on RACGP guidelines for T2DM management				
		Most recent HbA1c (self-report)				
		Cost of services				
Clinical services	*Health care utilisation*	GPAQ ver 2.1 [37]	✓		✓	Postal survey
		Clinical care agreements (annual cycle of care, General				
		Practice Management Plan, Team Care Arrangement)	✓	✓	✓	Postal survey
Cost Effective Analysis		# visits past 6 mths to diabetes clinician	✓	✓	✓	Postal survey
		# visits past 6 mths to other clinicians	✓	✓	✓	
		# visits past 6 mths for emergency/acute care	✓	✓	✓	
		# overnight stays past 6 mths in hospital (related to your diabetes)	✓	✓	✓	
Peer Training/ Quality Improve.	*Training effectiveness*	Usefulness of training		✓	✓	Postal survey
		Extent of content covered				
Process Evaluation		17 item assessment with 3 additional questions regarding most helpful, least helpful and suggestions to improve		✓	✓	Postal survey
		+ 2 questions asking availability of participant to other group members [38-40]				

The primary outcome measure is cardiovascular disease (CVD) risk using the UKPDS risk calculation [16]. People with diabetes are already at higher risk of CVD than the general population without diabetes. We consider that a 10% reduction in risk will be clinically significant, if we assume that the average risk for our participants is likely to be 20 – 25% in line with that in a sample with type 2 diabetes from Australian general practice [41]. Age at diagnosis, sex, ethnic group, smoking status, HbA1c, systolic blood pressure and total cholesterol/HDL ratio will be used in the UKPDS equation to determine CVD risk at baseline and 12 months [16]. Changes in the CVD risk over time as well as changes in waist circumference, body mass index (BMI), weight, and lipid profile will be used to assess diabetes self-management post intervention. Quality of life (AQoL [27] & EQ-5D[28,29]), depression (PHQ9, [32]) diabetes distress screening [30,31], self-care activities [23,24], medication adherence [25,26], food, smoking and alcohol intake [22], current support systems [34], known co-morbidities associated with diabetes, utilization of and satisfaction with available health services [37], diabetes knowledge using the Michigan Diabetes Research and Training Center Brief Diabetes Knowledge Test with modification to Australian context [35], health literacy [33] and confidence of diabetes management [36] are measured at baseline, six and 12 months.

### Program evaluation

Glasgow’s RE-AIM framework is being used to evaluate the program [42]. We are evaluating individual, group, and system level measures to assess the success of the program in achieving the key functions of peer support as specified by the global Peers for Progress Program Center [11] i.e. Assisting daily management, improving linkage to clinical care, providing social and emotional support and provide ongoing support. A process evaluation will determine the implementation fidelity of the trial and will assist in future refinements of the Aust PfP-DP.

#### Group-level measurements

In addition to individual-level measurements as outlined in Table 1, we will also measure group- and facilitator-level outcomes, including group effectiveness, satisfaction of group members and peer supporters and team dynamics, using a range of questions assembled in collaboration with the global Peers for Progress group [11] and based on items generated by Fisher in the Diabetes Initiative [43] and items from resources and supports for self-management (RSSM) and Patient Assessment of Chronic Illness Care (PACIC) [38-40]. Participants and supporters in the intervention arm are asked to complete an evaluation of the resources, health care providers who visited the groups and group meetings and perceptions of support received by supporters or other group members.

#### System-level evaluation

Feasibility of further dissemination and implementation of the Aust PfP-DP will be evaluated according to the five key dimensions of the RE-AIM framework which includes systematic measurement of internal validity (i.e. the ability of the intervention to produce a sustained change in patient health behaviours, including **E**ffectiveness and **M**aintenance) and external validity (i.e. the potential for the intervention to be generalized to other settings including **R**each, **A**doption, and **I**mplementation) [42]. Outcomes such as increased utilisation of DA-Vic resources, memberships and expansion of groups as a result of the intervention will also be assessed.

### Economic evaluation

The economic evaluation of the Aust PfP-DP will evaluate whether the program delivers ‘value-for-money’. This will be undertaken through a ‘trial-based evaluation’ (costs and outcomes exactly as per the trial), as well as a ‘modelled economic evaluation’, which will extend the target population, time horizon and decision context.

The cost data will also be combined with the change in the quality of life score for participants using the AQoL-8D [27] in both the trial-based and modelled evaluations. This will be helpful to consider value-for-money against a reference threshold (e.g. $50,000 per QALY).

The modelled evaluation will use the UKDPS outcomes model [44] to translate the changes in clinical outcomes observed over the relatively short time horizon of the study into potential lifetime reductions in cardiovascular and other diabetes related risks. The cost implications of the changes in health status will be estimated by drawing on Australian disease specific health expenditure data.

### Data analysis

Analysis will be performed based on based on an intention-to-treat i.e. without regard to the compliance of individuals within their allocated study arm. Analysis of covariance (i.e. linear regression models for 12-month measurements with baseline scores and intervention arm as co-variates) will estimate the changes from baseline to 12 months that can be attributed to the peer support intervention. Analyses will be done firstly on all individuals who complete follow-up and secondly on all individuals who were randomized using multiple imputation principles to deal with the missing data in individuals who do not complete follow-up. All analyses will be carried out with Stata software. Regression analysis will be used to determine the extent to which a variety of individual-, group- and system-level characteristics are associated with effective implementation and outcomes.

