**Methods:**

A national database of Australians diagnosed with type 2 diabetes is being used to invite people in pre-determined locations to participate in community-based peer support groups. Peer supporters are self-identified from these communities. All consenting participants receive diabetes self-management education and education manual prior to randomization by community to a peer support intervention or usual care. This multi-faceted intervention comprises four interconnected components for delivering support to the participants. (1) Trained supporters lead 12 monthly group meetings. Participants are assisted to set goals to improve diabetes self-management, discuss with and encourage each other to strengthen linkages with local clinical services (including allied health services) as well as provide social and emotional support. (2) Support through regular supporter-participant or participant-participant contact, between monthly sessions, is also promoted in order to maintain motivation and encourage self-improvement and confidence in diabetes self-management. (3) Participants receive a workbook containing diabetes information, resources and community support services, key diabetes management behaviors and monthly goal setting activity sheets. (4) Finally, a password protected website contains further resources for the participants. Supporters are mentored and assisted throughout the intervention by other supporters and the research team through attendance at a weekly teleconference. Data, including a self-administered lifestyle survey, anthropometric and biomedical measures are collected on all participants at baseline, 6 and 12 months. The primary outcome is change in cardiovascular disease risk using the UKPDS risk equation. Secondary outcomes include biomedical, quality of life, psychosocial functioning, and other lifestyle measures. An economic evaluation will determine whether the program is cost effective.

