### Study design and setting

The study is a cluster randomized controlled evaluation of a group-based peer support program, implemented and reported in accordance with the requirements of the CONSORT statement [17] and its extension to cluster randomized trials [18]. The study is being conducted in Victoria, Australia, a state that is divided into 79 local government areas (LGAs) within five regional and three metropolitan health regions. Community (defined as a post code area) peer support groups consisting of 10 – 12 participants are recruited, undergo baseline assessment, and then all participants are offered the opportunity to attend a one day diabetes self-management education (DSME) program to ensure that the intervention group does not simply use the sessions to obtain diabetes education rather than peer support. Finally, the groups are randomized to either an intervention arm or usual care arm with group postcode location being the unit of randomization. Groups assigned to the intervention arm participate in the peer support program for 12 months, while those assigned to the control arm continue with their usual care. Figure 1 is a CONSORT diagram of the study design. 

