### Sample size calculations

Sample size was determined by a requirement to have sufficient power to detect a meaningful difference between intervention and control group means of participant UKPDS score changes from baseline to 12 months. During the study, both groups will age by 1 year, which will increase their UKPDS risk calculation by identical amounts [16]. We anticipate this increase would be offset by reductions due to improvements in systolic blood pressure, total cholesterol/HDL cholesterol ratio, HbA_1_C, or smoking status. Assuming a standard deviation of 5% in baseline to 12 month UKPDS changes in both groups, 100 individuals per study arm with 12 month follow-up are required to provide 80% power to detect, with a 2 sided p-value of 0.05 for significance, a mean reduction of cardiovascular risk in the peer support arm that is 2% greater than any mean reduction in the usual care arm. The clustering of individuals by actual peer group (intervention arm) or future group (usual care arm) was not adjusted for because the comparisons across clusters are within-person changes over time and previous studies of UKPDS change in similar clusters found no clustering effects. Hence 12 groups and 120 participants per arm are required at baseline.

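### The stated treatment comparison makes no allowance for the randomised postcode group, so type I error exceeds 5% if outcomes are correlated within groups beyond what health region explains

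*Protocol article*

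**What the plan says.** Under Study design and setting, "the groups are randomized to either an intervention arm or usual care arm with group postcode location being the unit of randomization". The same section commits the trial to the CONSORT statement and its cluster extension. Under Allocation, randomisation is balanced within health regions of two or four groups. The Abstract describes delivery in groups: "Trained supporters lead 12 monthly group meetings".

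Data analysis specifies an analysis of covariance, described as "linear regression models for 12-month measurements with baseline scores and intervention arm as co-variates". It is to be run first on completers and then on all randomised individuals with multiple imputation. The section does not separate primary from secondary outcomes. It mentions no group effect, cluster-robust variance or cluster-level summary, and health region is not a covariate.

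The only explicit statement about clustering is under Sample size calculations: "The clustering of individuals by actual peer group (intervention arm) or future group (usual care arm) was not adjusted for". Two reasons are offered. One is that what is compared is each person's own change. The other is that "previous studies of UKPDS change in similar clusters found no clustering effects". No ICC or interval is given there.

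**The concern.** When groups are randomised, the precision of the arm comparison depends on how much group means vary, not only on how much individuals vary. A regression that counts each participant as independent understates the standard error whenever members of a group resemble one another in the baseline-adjusted outcome.

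This trial has a plausible source of such resemblance. Intervention members share a supporter and a year of meetings, and under Intervention condition each group shapes its own meeting content and arranges its own visits from health professionals. A few successful groups could then produce a nominally significant result. The primary p-value and confidence interval are exposed, and so are those for quality of life, distress, self-care and the other secondary outcomes.

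**Working it through.** **Inputs from the protocol article.** Difference 2 and SD of change 5 (percentage points of UKPDS risk), two-sided alpha 0.05, power 80%, 100 completers per arm, 12 groups and 120 participants per arm at baseline (Sample size calculations). The Figure 2 legend gives the same total of groups: 4 regions × 2, plus 4 in Geelong, plus 3 metropolitan regions × 4 = 24, in 8 health regions. Completers per group: m = 100/12 = 8.33.

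**Reproducing the plan's figure.** n per arm = 2 × [5 × (1.960 + 0.842)/2]² = 98.1, so 99 by the normal approximation. The t-based calculation gives 100. Allowing for one-sixth loss, 100/(5/6) = 120. The plan's figures are therefore reproduced, but only with a design effect of 1, that is, an ICC of 0.

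**Assumption.** The article gives no ICC, so a range from 0.01 to 0.10 is used for the baseline-adjusted outcome.

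**No clustering between regions.** Design effect DE = 1 + (m − 1) × ICC. The naive SE divided by the true SE is 1/√DE. Actual type I error = 2 × [1 − Φ(1.96/√DE)].

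| ICC | DE | SE too small by | Type I error |
|---|---|---|---|
| 0 | 1.00 | 0% | 5.0% |
| 0.01 | 1.07 | 3.5% | 5.9% |
| 0.02 | 1.15 | 6.6% | 6.7% |
| 0.05 | 1.37 | 14.5% | 9.4% |
| 0.10 | 1.73 | 24% | 13.7% |

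Simulating the stated analysis of covariance with 24 groups of 8 (20,000 runs per setting) gave 4.8%, 5.6%, 6.6%, 9.2% and 13.3%.

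**Allowing for the regional stratification.** Variation between regions is balanced across arms by design, so it does not add to the variance of the arm difference. If half the clustering is regional, the variance ratio becomes 1 + (m/2 − 1) × ICC = 1.03, 1.06, 1.16 and 1.32, and the same formula gives 5.4%, 5.7%, 6.9% and 8.8%. Simulation of the stratified design gave about 5.3%, 5.5%, 6.6% and 8.6%. If all of it is regional, the ratio is 1 − ICC, which is below 1, and there is no inflation.

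**Clustering in the intervention arm only** (usual care groups do not meet). Averaging DE over the arms gives 1 + (m − 1) × ICC/2. Type I error is then 5.9% at ICC 0.02, 7.2% at 0.05 and 9.4% at 0.10, with no regional share.

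**Cost in precision of a correct analysis.** On 22 df (24 groups less 2 arms) the critical value is 2.074, against 1.972 on the 198 df of an individual-level comparison. Relative interval width = (2.074/1.972) × √DE, which gives 1.09, 1.13, 1.23 and 1.38 at ICC 0.01, 0.02, 0.05 and 0.10. Power with 100 completers per arm on 22 df is 74.2%, 71.4%, 63.8% and 53.8%.

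**The case against.** The article does give its reasons. It says change is measured within person and that earlier studies in similar clusters showed no clustering of UKPDS change. If the ICC is truly zero, the stated model is valid at 5%. Those studies are not at hand, so their evidence cannot be judged here, and the higher ICCs in the table are assumptions. This limits the size of the claim but does not rescue the model. Adjusting for baseline removes stable differences between groups, not correlation in change that arises during follow-up. Failing to find clustering elsewhere does not establish an ICC of zero among people sharing this intervention, and the remark covers only one outcome.

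It can also be said that the model sentence names covariates, not a variance estimator, that the no-adjustment sentence concerns sample size, and that the commitment to the cluster extension of CONSORT might imply more. Cluster-robust errors would be compatible with the wording. That is fair, so non-adjustment is a reading of the text. It is the natural one, because the only reasoning about clustering in the article argues against adjustment.

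Stratification by region is a real offset and is built into the figures above.

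Two stronger inferences are not supported. A reader might conclude that the false-positive rate certainly exceeds 5%, but this depends on a positive within-region ICC, which the article neither gives nor rules out. A reader might also extend the fault to the last sentence of the section, "Regression analysis will be used to determine the extent to which a variety of individual-, group- and system-level characteristics are associated with effective implementation". The article does not state the unit of analysis of that regression, and its program evaluation includes group-level outcomes, so a group-level analysis would fit the text equally well.

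**Conclusion.** The concern holds conditionally. As written, the treatment comparison makes no allowance for the unit of randomisation, and the reasons offered do not justify leaving it out. If any group correlation exists within region, standard errors are too small and type I error is above the nominal 5%. Because groups are small, the excess is modest at ICC 0.01 to 0.02: under two percentage points with no regional share and about half a point or less with half regional. At ICC 0.10 with no regional share, the error rate is more than doubled. The sizes rest on the assumed ICC range, 12 groups per arm, about 8.3 completers per group and the share of clustering that lies between regions. The article settles neither the ICC nor that share. An analysis by group is valid whether or not the ICC is zero; the stated one is valid only if there is no within-region group correlation.

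**What to change.** In Data analysis, specify for the primary and secondary outcomes a linear mixed model of the 12-month value on arm, baseline value and health region, with a random intercept for group and a small-sample degrees-of-freedom correction (Kenward-Roger or Satterthwaite). An equivalent cluster-level analysis is acceptable if its degrees of freedom are reduced for region: with eight regions, 24 − 1 − 1 − 7 = 15, not 22. Use the same model in the analysis of imputed data. Report the observed ICC for each outcome. A group variance that differs by arm can be a sensitivity analysis, but with 12 groups per arm it would be poorly estimated, so it should not be required.

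No new data are needed, since group membership is known from randomisation. The cost is precision. If clustering exists, intervals are wider and power is lower. On 22 df and with no regional share, intervals are about 9–13% wider at ICC 0.01–0.02, 23% at 0.05 and 38% at 0.10. About 5% of that widening comes from the degrees of freedom alone. This is the precision the design has, and the unadjusted model would hide it.

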**Figure 2 F2:**
[figure not shown]
**Australasian Peers for Progress Diabetes Project Group locations in Victorian Health regions****.** Two locations were selected for randomisation in four of the five rural health regions. The regional centre of Geelong in the rural health region of Barwon South Western and each of the three metropolitan health regions had sufficient population and area to support the selection and randomisation of four group locations. An additional group was initiated as a pilot group in the western Metropolitan health region.

Prospective participants, enrolled on the NDSS database for more than 1 year, who indicated willingness to be contacted for research purposes, are resident within the selected location, and are aged between 25 – 75 years are invited by mail to contact the project team if interested in receiving further information about participating in the study as a peer supporter or as a group member. General Practitioners (GPs), community health centres, pharmacies, diabetes clinics, podiatrists, optometrists and any active DA–Vic ComNet groups or other community based groups within the selected locations are also targeted with posters and brochures to increase study exposure.

Self-identified peer supporters and participants with an interest in the project are sent comprehensive explanatory statements, outlining the aims of the study and the randomisation process. Participants are asked to return a signed informed consent indicating their agreement to participate whilst acknowledging their ability to withdraw if desired.

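### The plan puts a completers-only analysis first under an intention-to-treat label, names no primary analysis, and plans no 6-month risk although its changing inputs are scheduled then

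*Protocol article*

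**What the plan says.** The Data analysis section of the protocol article bases the analysis on "an intention-to-treat i.e. without regard to the compliance of individuals within their allocated study arm". The model is analysis of covariance, described as "linear regression models for 12-month measurements with baseline scores and intervention arm as co-variates". Two analysis sets follow in a fixed order: "Analyses will be done firstly on all individuals who complete follow-up and secondly on all individuals who were randomized using multiple imputation principles". The imputation is meant for people lost before the end of follow-up. Neither analysis is called primary, and the variables of the imputation model are not listed.

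On the outcome, the Data collection and outcome measures section lists the risk inputs as age at diagnosis, sex, ethnic group, smoking, HbA1c, systolic blood pressure and lipid ratio. On timing it says: "total cholesterol/HDL ratio will be used in the UKPDS equation to determine CVD risk at baseline and 12 months". In Table 1 the row "HbA1c,Total Cholesterol(TC), TC/HDL ratio" is ticked at baseline, 6 and 12 months, as are the rows for blood pressure and smoking.

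**The concern.** If the two analyses disagree, the article does not say which one tests the hypothesis in Study aims. Two features make completers look like the working primary set: they come first, and the Sample size calculations section powers the trial on people with 12-month follow-up.

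The arms are also handled differently for a year. Intervention participants have monthly meetings, reminders, contact from supporters and a newsletter. Usual-care participants receive copies of their own results. Reasons for leaving could therefore differ by arm. If they also relate to how people were doing, those who complete are no longer a randomised comparison.

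The second analysis protects against this only if the imputation knows something about leavers that the completers' model does not. The completers' model already conditions on baseline risk and arm. Imputing 12-month risk from those two variables alone uses the same information and should give essentially the same estimate. For people lost between 6 and 12 months, the natural extra information is their 6-month risk, and the article does not plan to calculate it.

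**Working it through.** **1. The plan's own sample size.** Inputs from Sample size calculations: difference 2 points, SD of change 5 points, two-sided 0.05, power 80%, equal arms.

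- n per arm = 2 × (1.960 + 0.842)² × 5² / 2² = 2 × 7.849 × 6.25 = 98.1, rounded up to 99. The plan states 100, so it reproduces.
- Power at 100 per arm: SE = 5 × √(2/100) = 0.707; 2/0.707 − 1.960 = 0.868; power 80.7%.
- Implied loss: 1 − 100/120 = 16.7%. The article states no attrition rate; this is inferred from its two figures.

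**2. Can a 6-month risk be calculated?** The inputs that change are HbA1c, TC/HDL ratio, blood pressure and smoking, and all four are ticked at 6 months. Age at diagnosis appears ticked at baseline and 6 months. Sex and ethnicity appear ticked at baseline and 12 months only, but they are fixed. Current age follows from dates. So the score can be calculated from data already scheduled.

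**3. What completers can hide (illustration).** Suppose completers show the 2-point effect and 20 of 120 per arm are lost. If the effect in those lost is x, the all-randomised effect is (100 × 2 + 20 × x)/120. Power is for 120 per arm at that effect, SE = 5 × √(2/120) = 0.645.

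| Effect in those lost (assumed) | All-randomised effect | Power |
|---|---|---|
| 2 | 2.00 | 87% |
| 1 | 1.83 | 81% |
| 0 | 1.67 | 73% |
| −2 | 1.33 | 54% |

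With x = 0 the completers' figure overstates by 2.00/1.67 = 1.20, that is 20%. This follows entirely from the assumed x.

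**4. Simulation of the two estimators.** Assumptions: 120 per arm; baseline risk mean 22.5 (midpoint of the 20–25% the article assumes) with SD 10; SD of change 5; true effect −1 at 6 months and −2 at 12 months; correlation of the 6- and 12-month changes 0.5 or 0.7; no clustering; 4,000 trials per setting. Where dropout depends on interim response, its log-odds move by 0.7 per SD of the 6-month change, with poor responders more likely to leave the intervention arm. Imputation was by conditional mean from baseline, arm and 6-month risk, with interactions of arm with both risks. This approximates the point estimate of multiple imputation. Ranges cover the two correlations.

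| Dropout | Missing | Completer ANCOVA | Imputation with 6-month value |
|---|---|---|---|
| Random | 15% | −2.00 | −1.99 to −2.00 |
| Related to 6-month change, alike in both arms | 18% | −2.00 to −2.02 | −1.99 to −2.02 |
| Related in the intervention arm only | 16–17% | −2.29 to −2.38 | −1.98 to −2.01 |
| Related, opposite directions by arm | 17–18% | −2.57 to −2.79 | −1.98 to −2.00 |

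The bias in the last two rows runs from 2.29 − 2.00 = 0.29 to 2.79 − 2.00 = 0.79 points. The SD of the estimate across simulated trials was about 0.7. With the dropout mechanism reversed, the bias would change sign by symmetry.

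**The case against.** The strongest reply is that the wanted analysis is already there. The article explains intention-to-treat only as disregarding compliance, completers analysed as allocated meet that wording, and an all-randomised analysis with multiple imputation is promised. This stands. A reader might infer that the plan contradicts its own intention-to-treat claim, but the text does not support that. The weakness is the order and the missing designation.

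Secondly, the contents of an imputation model usually belong in an analysis plan, which is not shown. This also stands. A reader might infer that the 6-month values are excluded, but nothing in the article excludes them from the imputation. Nor is leaving out a 6-month risk an error in itself, because the stated comparison is baseline to 12 months. What remains is that the article fixes the calculation times for risk and a two-time-point model, and so passes over the information that would make the second analysis worth having. The label of primary analysis might also sit in an analysis plan, but the article chose to state an order and put completers first.

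Thirdly, the article gives no data on dropout by arm, and usual-care participants receive their own results at each time point, so retention need not be one-sided. This stands and makes the bias conditional.

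Finally, a reader might infer that the completer set would admit the pilot group, since only the second set is worded as randomised. The Figure 2 legend says: "An additional group was initiated as a pilot group in the western Metropolitan health region". The locations it lists for randomisation total 4 × 2 + 4 + 3 × 4 = 24, which matches the 12 groups per arm in Sample size calculations. The pilot is separate from these, and nothing places it in an arm or in an analysis. That reading is not supported.

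**Conclusion.** The point holds in a limited form. Under an intention-to-treat label, a completers-only ANCOVA comes first, the all-randomised analysis second, and neither is primary. The plan does not provide for a 6-month risk that its own schedule allows.

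The size depends on dropout. With about one in six lost, as the sample size implies, the completers' estimate is essentially unbiased if loss is random or acts alike in both arms. If loss is related to the 6-month change and differs by arm, a true 2-point reduction was overstated by about 0.3 to 0.8 points, or 15% to 40%, under the mechanisms assumed. The 20% figure in the working is an illustration, not a forecast. It would be too strong to say that the result will favour the programme: the direction depends on who leaves which arm, and the article does not say. The near-complete removal of bias by imputation also rests on dropout depending on values that were observed at 6 months. It would not extend to people lost before that visit or to loss driven by later, unobserved change.

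**What to change.** In Data analysis, name one primary analysis: all individuals in the randomised groups, analysed as allocated, with the contrast at 12 months. Make the completers' analysis a sensitivity analysis.

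Then do one of the following:

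- State that the imputation model includes the 6-month UKPDS risk or its components, together with arm, health region and group.
- Fit a mixed model to risk at baseline, 6 and 12 months, with the arm contrast taken at 12 months.

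In Data collection and outcome measures, add 6 months to the times at which risk is calculated, as supporting information for the 12-month comparison rather than a new endpoint.

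The cost is a few sentences and modest extra programming. No new data are needed, and the sample size does not change.
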